#### Planned analysis

The results in each cluster would be analyzed on the basis of “intention to treat”. This means the quality of care and service utilization outcomes of each patient will be counted in the intervention for the cluster, regardless of their actually accepting or availing the offered services.

#### Planned statistical tests

Cluster and individual level analysis will be done on SPPS version 17. Histograms will be made for the continuous variables e.g. age, systolic blood pressure, diastolic blood pressure, fasting blood glucose, HbA1c etc.

Descriptive statistics will be computed: proportion for categorical variables, mean and standard deviation for continuous variables having normal distribution, median and inter quartile range for continuous variables having skewed distribution.

a. Difference of mean systolic blood pressure at baseline and then at 15 months of follow up between the intervention and the control arm will be measured by independent t-test. Difference of mean systolic blood pressure at baseline and at 15 months of follow up in the intervention arm/control arm will be measured by the paired sample t-test. Mean change of systolic blood pressure between intervention and the control arm will be measured by t-test. P-value of < 0.05 will be considered significant.

b. Difference of mean HBA1c at baseline and then at 15 months of follow up between the intervention and the control arm will be measured by independent t-test. Difference of mean HBA1c at baseline and at 15 months of follow up in the intervention arm/control arm will be measured by the paired sample t-test. Mean change of HBA1c between intervention and the control arm will be measured by t-test. P-value of < 0.05 will be considered significant.

c. Difference of mean total cholesterol levels at baseline and then at 15 months of follow up between the intervention and the control arm will be measured by independent t-test. Difference of mean total cholesterol levels at baseline and at 15 months of follow up in the intervention arm/control arm will be measured by the paired sample t-test. Mean change of total cholesterol levels between intervention and the control arm will be measured by t-test. P-value of < 0.05 will be considered significant.

d. Proportions of adult Type 2 diabetes patients having htn control (<140/90) in the two arms will be compared by conducting chi-square test. P-value of < 0.05 will be considered significant.

e. Residual confounding will be taken care of by multivariable regression (MLR)analysis. Strartified MLR will be done with the different groups of medications being as different strata eg, Beta blockers, ACE inhibitors, ARBs, Calcium channel blockers etc. being as different strata. Results will be presented in a stratified analysis. This will take care of confounding my different effects on BP from different groups of anti hypertensive drugs.

f. Incremental cost and effect will be calculated for the intervention and the control arms and subsequently cost: effect ratio will be calculated.

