### Primary objective

To compare the mean change in systolic blood pressure (10 mmHg) in adult patients (>25 years) receiving enhanced CVD-HTN care package with the mean change in systolic blood pressure (5 mmHg) for those receiving routine care at the private facilities in Punjab.

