#### Inclusion/exclusion criteria

Among these private facilities ,all newly diagnosed hypertensive (systolic blood pressure >140 mm Hg, diastolic blood pressure >90 mm Hg) male and female patients aged 25 years or more from the catchment population of the respective facility will be included, after an informed consent. The patients to be excluded from the trial are: a) pregnant women, b) persons with advanced chronic disease, c) person with conditions that cause secondary hypertension, d) person with known history of hypertension and/or CVD treatment in the past, e) person not likely to stay in the area for the required follow-up period of 15 months.

Patients who are pregnant and have hypertension will be referred to a gynecologist, patients with advanced chronic disease to a general medical practitioner, and those with a known history of hypertension and/or CVD treatment in the past will be referred to a cardiologist. Only patients who are new cases of hypertension are included in the trial. People with known hypertension are excluded from the trial as they would already be on some sort of antihypertensive drug regimen which may mask the effects of our intervention.

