### Statistical considerations

#### Sample size

A total of twelve clusters^c^ (i.e. six clusters in each trial arm) will be included in the study, with a minimum of 76 patients recruitment in each cluster and a total of 912 patients in the trial. The assumptions are: a) an intra-class correlation coefficient (ICC) of 0.02, b) design effect of 2.5 [4], c) and standard deviation of blood pressure as 11 mm [5] d) lost to follow-up of 25%. This sample size will give 94% power using 5% level of significance for detecting an assumed difference in the mean change of systolic blood pressure of 6 mm Hg between the intervention and the control arm [6,7].

For a sub group analysis of hypertensive patients with concomitant type-II diabetes, the main assumption is that 27.6% of the recruited hypertensive will have type-II diabetes i.e. 21 patients out of 76 hypertensive recruited at each clinic will be have diabetes [3]. The proposed sample size will give 86% power using 5% level of significance for detecting an assumed difference in mean change of HbA1c of 1% [8,9] between the intervention and the control arms. The assumed standard deviation of HbA1c is 2% [10], and intra-cluster correlation is 0.02 [6,7].

For a sub group analysis of hypertensive patients with concomitant hyper-cholesteremia, the main assumption is that 39.3% of the recruited hypertensive will have hyper-cholesteremia i.e. 30 patients out of 76 hypertensive recruited at each clinic will be have hyper-cholesteremia [3]. The proposed sample size will give 100% power using 5% level of significance for detecting an assumed difference of 4.9 mg/dl [11] between the group means. The assumed standard deviation is 2.9 mg/dl [11], and intra-cluster correlation is 0.02 [6,7].

For a sub group analysis those hypertensive patients who smoke, the main assumption is that 34.5% of the recruited hypertensive will be tobacco smokers i.e. 27 out of 76 hypertensive recruited at each clinic will be smokers [3]. The proposed sample size will give 100% power using 5% significance level for detecting a difference between the group proportions of 0.33 when the intra-cluster correlation is 0.02 [6,7].

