### Addressing bias, error and limitations

Comparing the socio-demographic and health services profiles of the private facilities does not indicate any significant difference that can potentially lead to differences in care seeking behavior and/or quality of service. The proposed cluster randomization is expected to address the potential selection bias across the two trial arms.

The process of equal screening and diagnosing training in both arms will lead to similar disease intensity patients being recruited in both arms. Although similar training of health professionals in both arms in regards to better screening this will eliminate selection bias, it will lead to a inability to measure ‘case detection rate’ due to better screening.

The lack of masking (blinding) could introduce bias through two routes i.e. “incorrect measurement” and “leakage” from one group to another. There was a possibility of incorrect measurement of “blood pressure outcomes” by the facility doctor, who is aware of the intervention allocation. This possibility of measurement bias will be reduced through an unrelated external BP monitoring doctor who is unaware of the intervention allocation. Contamination across clusters is prevented by keeping a minimum distance between clusters.

The proposed randomization does not allow asking and responding to individual patient preferences. So the trial will not answer the question what would happen if health services are able to offer intervention according to individually tailored patient needs/ convenience. Further work will be needed to test the approaches sensitive to individual preferences, in the local programme setting.

The proposed method of randomization, ie concealed simple randomization has its own limitations. This method does not address the balance of baseline covariates. An alternative approach could have been addresses the need to control and balance the influence of covariates by using stratified randomization. This method can be used to achieve balance among groups in terms of baseline characteristics (covariates) of health facilities based on socio demographics of catchment population they feed into, size of health facility, patient load etc. Different strata /blocks of health facilities may have been made and then simple randomization done in each strata to achieve a balance of covarites. This could have minimized the biased that simple randomization does not address.

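### Items a to c name no single primary comparison, use within-arm paired tests that cannot test the package, and omit baseline as a covariate

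*Protocol article*

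**What the plan says.** Item a of Planned statistical tests sets out three kinds of SBP test. The first is an independent t-test at each time point: "Difference of mean systolic blood pressure at baseline and then at 15 months of follow up between the intervention and the control arm". The second compares baseline with 15 months inside each arm, which "in the intervention arm/control arm will be measured by the paired sample t-test". The third is a between-arm t-test on mean change. The item closes with "P-value of < 0.05 will be considered significant". Items b and c repeat the set for HbA1c and total cholesterol. That is five P values per outcome and fifteen in all.

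Item e adds a multivariable regression for residual confounding, stratified by antihypertensive class. It does not name baseline SBP and is not presented as the main analysis.

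Other sections bear on which test decides. The Primary objective compares mean change between arms, 10 mmHg under the package "with the mean change in systolic blood pressure (5 mmHg) for those receiving routine care". The Sample size section powers the trial for "detecting an assumed difference in the mean change of systolic blood pressure of 6 mm Hg". The Abstract words the main outcome as a mean difference in SBP between arms, and the Secondary objectives list a mean SBP difference again.

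On who enters, Inclusion/exclusion criteria takes "all newly diagnosed hypertensive (systolic blood pressure >140 mm Hg, diastolic blood pressure >90 mm Hg". On balance, Addressing bias, error and limitations says: "The proposed cluster randomization is expected to address the potential selection bias across the two trial arms". The same section concedes that simple randomisation does not balance baseline covariates.

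**The concern.** Patients are enrolled because a reading is high, and they then start treatment. Regression to the mean and treatment should both lower SBP in either arm, and the protocol itself assumes a fall under routine care. A paired test asks whether SBP fell within an arm. It does not ask whether the package made it fall further.

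The two between-arm tests do address the package, but neither conditions on baseline. With twelve facilities allocated by simple randomisation and patients enrolled afterwards, some baseline difference between arms is to be expected. It moves the two tests in opposite directions: a higher baseline in one arm raises that arm's 15-month mean but exaggerates its fall. Since item a does not say which test decides, the same data could support two different answers.

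At stake are a clear primary result, some precision, and protection against reading a significant within-arm fall as evidence of effectiveness.

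**Working it through.** **Inputs from the Sample size section and the objectives.** SD 11 mmHg; ICC 0.02; 6 facilities per arm; 76 patients per facility (456 per arm); 25% loss, which leaves 57 per facility and 342 per arm; target difference 6 mmHg; expected changes 5 mmHg (control) and 10 mmHg (intervention). The design effect among completers is 1 + 56 × 0.02 = 2.12; at 76 per facility it is 2.5, as the protocol states.

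**Assumptions not in the documents.** The correlation rho between baseline and 15-month SBP is taken as 0.3 to 0.7 and the same at patient and facility level, with equal SDs at the two times.

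**1. The plan's own figure.** The protocol says: "This sample size will give 94% power using 5% level of significance". With 342 per arm, design effect 2.12 and SD 11, the standard error of the difference is 11 × √(2 × 2.12/342) = 1.22 mmHg. Two-sided power for 6 mmHg is then 99.8% (normal) or 99.2% (t on 10 df). A figure near 94% appears only if the SD of change is taken as 11√2 = 15.6, which gives 93.4%. This mismatch is a separate matter and nothing below depends on it.

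**2. Paired test in the control arm at a 5 mmHg fall.** Take 11 as the SD of change, which is exact at rho = 0.5.
- As planned, ignoring clustering: SE = 11/√342 = 0.595; ratio 5/0.595 = 8.4.
- With design effect 2.12: SE = 11 × √(2.12/342) = 0.866; ratio 5/0.866 = 5.8; power 99.4% even on 5 df.
- With a change SD of 15.6 and no clustering, the ratio is 5.9.
- The smallest change reaching P < 0.05 in the planned test is 1.96 × 0.595 = 1.2 mmHg.

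In simulated trials with a 5 mmHg fall in both arms and no package effect, both paired tests were significant in 100%. With no change in either arm, both were significant in only about 4%.

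**3. Chance baseline difference between arms.** SD = 11 × √(2 × 2.12/342) = 1.22 mmHg (1.15 if all 456 per arm are used). A 2-SD difference is about 2.4 mmHg. Only part of it reaches an estimate: rho × 2.4 for the 15-month comparison, and −(1 − rho) × 2.4 for the change score. For rho from 0.3 to 0.7 the shift is about 0.7 to 1.7 mmHg in size for either test, and opposite in sign.

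**4. Precision.** In units of the single-reading variance, the 15-month comparison has 1, the change score 2(1 − rho), and the baseline-adjusted comparison 1 − rho². The ratio of adjusted to change score is (1 + rho)/2, a saving of (1 − rho)/2.

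| rho | Saving v change score | Saving v 15-month only (rho²) |
|---|---|---|
| 0.3 | 35% | 9% |
| 0.5 | 25% | 25% |
| 0.7 | 15% | 49% |

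Simulated standard errors at rho 0.5 (6 + 6 facilities of 57) were 1.21 for 15-month only, 1.24 for change and 1.06 for adjusted.

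**5. False-positive rate.** If clustering is ignored, each between-arm test, adjusted or not, has a type I error of about 17 to 18% (2 × [1 − Φ(1.96/√2.12)] = 17.8%). At facility level it is about 5%. If either the 15-month test or the change test may be claimed, the rate is about 9% with clustering handled and about 30% without.

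**The case against.** The strongest reply is that the main comparison can be worked out. The Primary objective and the Sample size section both concern between-arm mean change, and the third test in item a is that comparison. This stands. The gap is that the analysis section does not designate it, while the Abstract's wording fits the 15-month test as well.

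Next, the change score already uses baseline by subtraction, an unadjusted change score is valid under randomisation, and power is ample. At rho 0.5 with true changes of 5 and 10 mmHg, facility-level power is 96.0% for change and 99.0% with adjustment. This stands too: the precision gain is worth having but does not rescue the trial. Item e might include baseline SBP, and the pilot phase allows the methods to be revised. Neither commits to it.

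Both arms receive the same screening training, and baseline BP is validated by a blinded external examiner. These measures reduce recruitment imbalance but do not remove chance imbalance among twelve facilities.

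A reader might infer four stronger claims that the documents do not support:
- That the paired tests will be significant whatever happens. This needs SBP to fall in controls, which the protocol assumes but cannot guarantee.
- That the full 2.4 mmHg, 40% of the target, enters the estimate. Only the fraction rho or (1 − rho) does, and it is chance variation that a correct standard error already reflects.
- That the protocol intends to claim effectiveness from a paired test. Nothing says so.
- That baseline adjustment alone prevents false claims. It does not, because type I error stays near 17 to 18% until clustering is handled.

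**Conclusion.** The point holds as a recommended improvement, not as a fatal flaw. Items a to c leave the primary test undesignated and include paired tests that, on the protocol's own 5 mmHg control change, are all but certain to be significant in both arms with or without a package effect (ratio 8.4, or 5.8 with the design effect, taking 11 mmHg as the SD of change). Baseline is not named as a covariate anywhere. The consequence is a shift of about 0.7 to 1.7 mmHg in the unadjusted estimates at a 2-SD chance imbalance, or 12% to 29% of the 6 mmHg target, and a variance 15% to 35% larger on the change score than it needs to be (as a share of the change-score variance). Both ranges rest on an assumed rho of 0.3 to 0.7. The direction of the precision gain holds for any rho between 0 and 1.

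**What to change.** Name one primary analysis: 15-month SBP regressed on arm and baseline SBP, with facility as a random effect and small-sample degrees of freedom. A baseline-adjusted facility-level analysis on about 10 df would serve equally well. The facility term and its degrees of freedom are an essential part of the change.

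Use the same form for HbA1c and total cholesterol. Drop the paired tests, and the separate baseline and 15-month t-tests, as tests of effect. Report baseline values and within-arm changes descriptively, without P values. Align the Abstract and the objectives with the chosen comparison.

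The cost is wording only. Recruiting participants already provides for baseline BP, HbA1c and cholesterol in both arms, and Phases of the trial sets aside the pilot for revising the statistical methods before patients are registered.

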**Methods/Design:**

A pragmatic cluster randomized trial, with qualitative and economic studies, will be conducted in Sargodha district of Punjab, Pakistan, from January 2012 to December 2016. At least 912 hypertensives will be registered in the two arms, six clusters per arm. The proposed cluster randomized controlled trial will evaluate the effects of delivering quality HTN-CVD care, through enabled private health care facilities, to achieve better case registration, adherence and hypertension control also blood glucose and serum cholesterol control. The trial will be conducted through the doctors and paramedics at private health facilities. Main outcomes are mean difference in Systolic blood pressure among the two arms. Secondary outcomes are mean change in total serum cholesterol levels and mean change in glycaemic control achieved in the adult hypertensive patients. Individual and Cluster level analysis will be done according to intention-to-treat.

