– Refine the case management guidelines/ materials Assess and shortlist the health facilities for possible inclusion in the trial. Randomization :The ASD central trial unit, under the supervision of Trial Steering Committee, will then randomize the facilities into two trial arms. Randomization preformed will be simple randomization. Each participating facility (cluster) will be given a unique ID which the investigators will be blinded to.12 different sheets of paper will be taken and the unique ID of each cluster will be written on the paper, which will be folded and sealed into an envelop.12 such sealed envelopes will be made. Then by a simple procedure, 6 sealed envelopes will be selected by hand picking them randomly from the pile of 12 sealed envelopes.6 will be hand picked for the intervention arm and 6 sealed envelopes for the control arm. The Steering committee will consist of a director, two people from ASD and two people from in-country (PMRC) and international partners (WHO).

– At least two doctors and two paramedics from each participating facility will be trained. The intervention facility staff will be trained on enhanced case management guidelines and materials including recording reporting and enhanced follow-up and referral, whereas the control facility staff will be trained only to register and report, use patient education brochure, and access HbA1c and cholesterol testing for trial patients.

– In the next 06 months of the trial implementation phase, the patients will be registered and enrolled in the trial, as per agreed protocols. During the period the baseline hypertension measurement will be validated by an external expert examination, kept blind to the trial arm as well as any previous measurements.

– The case management enhancement in the intervention arm will include: case management desk-guide for patient care, flip chart and brochure for patient education, mobile link for late patient retrieval, referral for advanced care (if needed), regular monitoring and support.

– Once the required number of trial patients is enrolled in the trial, the subsequent patients will receive HTN-CVD and associated care from the respective facility (as per prevailing case management protocols i.e. either intervention or control) but their results will not be included in the trial evaluation.

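### The listed between-arm tests carry no cluster adjustment, and the plan does not say whether the patient-level or the facility-level analysis decides; if the patient-level SBP test decides, its type I error is about 18–21.5% at the plan's own ICC

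*Protocol article*

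**What the plan says.** The unit of randomisation is the facility. Under Phases of the trial, the central unit "will then randomize the facilities into two trial arms". The Sample size section plans "six clusters in each trial arm", with "a minimum of 76 patients recruitment in each cluster and a total of 912 patients in the trial", and assumes "an intra-class correlation coefficient (ICC) of 0.02, b) design effect of 2.5".

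The Planned statistical tests section works outcome by outcome. Item a, on systolic blood pressure (SBP), lists an independent t-test between arms at baseline and at 15 months, a paired t-test within each arm, and then the comparison that matches the primary objective: "Mean change of systolic blood pressure between intervention and the control arm will be measured by t-test". Items b and c repeat this for HbA1c and total cholesterol. Item d covers BP control among patients with type 2 diabetes, whose proportions "in the two arms will be compared by conducting chi-square test". For each item, "P-value of < 0.05 will be considered significant". Item e adds multivariable regression without giving model terms.

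On the level of analysis, the abstract says "Individual and Cluster level analysis will be done according to intention-to-treat". Planned statistical tests opens with the same promise of both levels. Neither place links a level to a listed test or ranks the two.

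**The concern.** Patients of one facility share a practitioner and a catchment population, so their outcomes are correlated. The sample size recognises this, but no listed test does: there is no facility term, random effect, robust variance or design-effect correction. A t-test or chi-square test on individual patients treats them as independent. Its standard error is then too small by a factor of the square root of the design effect.

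The text commits to an individual-level analysis and leaves its standing open. Two analyses with quite different error rates are promised, and a conclusion could be drawn from either. The Discussion ties a showing of effectiveness to enabling the control facilities and to consulting on scale-up in 31 other districts, so a false positive on SBP would have consequences beyond this trial.

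**Working it through.** **Inputs.** From Sample size: 6 facilities per arm, m = 76 patients per facility, ICC 0.02, design effect 2.5, SD 11 mm Hg, 25% loss to follow-up. Loss leaves 0.75 × 76 = 57 per facility. The level is 5%. Sidedness is not stated, and two-sided is assumed.

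**The plan's own figures.**
- Total: 12 × 76 = 912. Reproduces.
- Design effect: DE = 1 + (m − 1) × ICC = 1 + 75 × 0.02 = 2.5. Reproduces. After loss, DE = 1 + 56 × 0.02 = 2.12.
- Power for 6 mm Hg, stated as 94%: does not reproduce at SD 11. The normal approximation gives 99.9% (76 per facility), 99.8% (57), or 99.5% (57 with DE held at 2.5). This is a separate matter and does not enter the type I error calculation.

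**Type I error of a patient-level test.** An unadjusted statistic has true variance DE instead of 1 under no effect, so

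α = 2 × [1 − Φ(1.96 / √DE)].

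The standard error is understated by 1 − 1/√DE: 1 − 1/√2.12 = 31% and 1 − 1/√2.5 = 37%.

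| Outcome (ICC 0.02) | m | DE | α, formula | α, simulation |
|---|---|---|---|---|
| SBP, all recruited | 76 | 2.50 | 21.5% | 21.7% |
| SBP, after loss | 57 | 2.12 | 17.8% | 18.0% |
| Diabetic subgroup, all recruited | 21 | 1.40 | 9.8% | 9.8% |
| Diabetic subgroup, after loss | 16 | 1.30 | 8.6% | 8.6% |
| Hypercholesterolaemic subgroup, all recruited | 30 | 1.58 | 11.9% | 11.8% |
| Hypercholesterolaemic subgroup, after loss | 22 | 1.42 | 10.0% | 10.1% |

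The simulation used 200,000 trials per row with 6 equal-sized facilities per arm, normal outcomes and a pooled t-test on individuals. In the same simulations a t-test on the 12 facility means (10 df) rejected in 5.0–5.1% of trials.

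The subgroup sizes are the plan's own 21 and 30 per facility, reduced by 25% for loss (0.75 × 21 = 15.75; 0.75 × 30 = 22.5). The diabetic rows apply to HbA1c. They also approximate item d, which is restricted to diabetic patients, if its ICC is also 0.02. The cholesterol rows apply only if item c is limited to the hypercholesterolaemic subgroup, as in the power paragraph. Item c itself sets no such limit, and the secondary objective refers to hypertensive patients generally. If all are analysed, the SBP rows apply.

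**Sensitivity to the ICC** for SBP, 57 to 76 per facility (simulation; ICCs other than 0.02 are assumptions):

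| ICC | α |
|---|---|
| 0.005 | 8–9% |
| 0.01 | 12–14% |
| 0.02 (plan) | 18–21.7% |
| 0.05 | 32–37% |

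At ICC 0.05 and m = 57 the formula gives 31.5% (DE 3.80), so the range across methods is about 31–37%.

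**Power of the facility-mean test** for 6 mm Hg (noncentral t, 10 df): at SD 11 it is 99.7% (76 per facility), 99.2% (57), or 98.2% (57 with DE 2.5).

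**The case against.** The strongest reply is that the primary t-test need not be a patient-level test. The sentence quoted from item a names no unit, both the abstract and the methods promise a cluster-level analysis, and the Planned analysis section speaks of analysing results by cluster. A t-test on 12 facility means is also a t-test, and it is valid. This stands against a stronger reading that a reader might infer, namely that the primary test simply has an 18–21.5% false-positive rate. The document does not settle the level, so that rate is conditional.

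It does not remove the concern. An individual-level analysis is also promised. A chi-square test comparing proportions of patients is naturally a patient-level test. Nothing says that the cluster-level result prevails.

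A second reply is that model detail belongs in an analysis plan that is not shown. That is fair for covariates, degrees of freedom and the terms of the item e regression. It does not cover the tests that the article does state, outcome by outcome and with a significance threshold; run on patients, these give wrong P values.

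Third, Phases of the trial lets the pilot revise the statistical methods where needed. That permits a correction but does not make one.

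Finally, the rates above concern between-arm tests. The within-arm paired t-tests do not estimate the treatment effect, and these figures do not describe them.

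**Conclusion.** The point holds in conditional form. The plan sizes for clustering, lists only tests without cluster adjustment, and leaves open which level decides. If the patient-level test of SBP change decides, its type I error at ICC 0.02 is about 18% (57 per facility) to 21.5% (76 per facility), and nominal 95% intervals would cover about 78.5–82%. The corresponding rates are about 9–10% for the diabetic subgroup and 10–12% for cholesterol if restricted to the hypercholesterolaemic subgroup. If the facility-mean test decides, the rate is about 5%.

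These figures assume a two-sided test, equal facility sizes, and an ICC of 0.02 that applies to each analysed outcome, including the change scores. The inflation persists at lower ICCs: it is still 8–9% for SBP at 0.005. Because the primary inference is affected, this should be settled before analysis.

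**What to change.** In Planned statistical tests, state that one cluster-respecting analysis is primary and decides the conclusion. Either of these would do:

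- a t-test on the 12 facility means of SBP change, with 10 degrees of freedom; or
- a linear mixed model with a random facility effect and small-sample degrees of freedom.

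Use the same approach for HbA1c and cholesterol, and say which patients item c covers. For item d, compare facility-level proportions or use an equivalent cluster-adjusted method. State that unadjusted patient-level between-arm tests will not be used for inference.

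The change is one of wording; it needs no extra patients or facilities. For SBP, confidence intervals widen by a factor of about √2.12 = 1.46 to √2.5 = 1.58 relative to the unadjusted ones, plus a little more for 10 df. The sample size already includes the design effect, and at the stated SD of 11 the facility-mean test keeps 98–99.7% power. One caution: if the SD of the change were 11 × √2 = 15.6 mm Hg (an assumption that the document does not state), that power would be about 91% with 76 per facility, 88% with 57, or 82% with 57 and DE 2.5. The SD should therefore be confirmed when the pilot revisits the sample-size assumptions.

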### Research question

•How effective and feasible is to deliver and manage quality care for the control of selected cardiovascular diseases (i.e. hypertension, type-II diabetes, and hyper-cholesteremia) in adults (i.e. > 25 years), through enabled private health facilities as compared to current practice, in urban settings?

The control of selected cardiovascular diseases will be assessed by measuring change in blood pressure, blood glucose, and serum cholesterol.

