### Hypothesis

•The enabling of private health facilities for cardiovascular disease intervention for adult hypertensive patients will improve the control of hypertension by decreasing mean systolic BP by at least 6 mm Hg.

•The enabling of private health facilities for cardiovascular disease intervention for adult hypertensive patients will improve the control of Blood glucose (HbA1C < 7.5%) and serum cholesterol (<200 mg/dl) by at least 15% (as compared to the current practice).

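### The diabetes subgroup's only blood pressure test cuts BP at 140/90 and ignores baseline; a baseline-adjusted SBP comparison would probably have clearly more power

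*Protocol article*

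**What the plan says.** Planned statistical tests, item d: "Proportions of adult Type 2 diabetes patients having htn control (<140/90) in the two arms will be compared by conducting chi-square test". The rule attached to it is "P-value of < 0.05 will be considered significant". No other blood pressure comparison is written for patients with diabetes.

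Elsewhere the article treats blood pressure as a continuous quantity:

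- Research question: "The control of selected cardiovascular diseases will be assessed by measuring change in blood pressure, blood glucose, and serum cholesterol".
- Hypothesis: enabling the facilities "will improve the control of hypertension by decreasing mean systolic BP by at least 6 mm Hg".
- Planned statistical tests, item a (all patients): "Mean change of systolic blood pressure between intervention and the control arm will be measured by t-test".
- The Primary objective, the first Secondary objective and the Sample size section are also framed in mean SBP or its change.

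On the subgroup's size, Sample size assumes "27.6% of the recruited hypertensive will have type-II diabetes i.e. 21 patients out of 76 hypertensive recruited at each clinic". The only power figure given for diabetics is 86%, and it is for HbA1c. The secondary objective for diabetics is likewise about HbA1c.

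**The concern.** Item d changes scale without giving a reason, and does so in a small subgroup. A continuous measure taken at baseline and at 15 months becomes a yes/no result at one time point, tested at the 5% level with the baseline value left out. Dichotomising discards information on how far each patient moved, and omitting baseline discards the precision it could add.

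Type 2 diabetes is one of the conditions the care package is meant to cover, so readers will look at this result. If the package lowers SBP in diabetics by the 6 mmHg assumed for the trial, a non-significant item d could be taken to mean that it does not work on blood pressure in them. The result would also depend on how far above 140 patients start: the same 6 mmHg moves fewer patients across the line when baseline pressure is higher.

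**Working it through.** **Inputs from the article.** "A total of twelve clusters", six per arm; 21 diabetics per cluster; 25% loss to follow-up; ICC 0.02; SD of blood pressure 11 mmHg; difference 6 mmHg; 5% significance.

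**Assumptions added here.** The test is two-sided. The SD of 11 is that of final SBP, since the article does not say which SD it is. Mean baseline SBP is not given and is taken as 150, 155 or 160 mmHg, entry being above 140. The 6 mmHg is split as falls of 11 and 5 mmHg. Both analyses are cluster-adjusted with 12 − 2 = 10 degrees of freedom.

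**Effective size per arm.** Design effect = 1 + (m − 1) × 0.02. (The article's 2.5 belongs to m = 76.)
- m = 21: 1.40; 6 × 21 / 1.40 = 90.0.
- m = 16 (21 × 0.75 = 15.75, rounded): 1.30; 6 × 16 / 1.30 = 73.8.

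**The plan's own subgroup figure.** HbA1c, 1% difference, SD 2%, m = 16: 1 / (2 × √(2/73.8)) = 3.04; Φ(3.04 − 1.96) = 86.0%, matching the stated 86%. With m = 21 and a t-test on 10 df it is 85.5%. The subgroup inputs are therefore being read as intended.

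**Baseline-adjusted SBP.** The residual SD is 11 × √(1 − ρ²), where ρ is the correlation between baseline and final SBP, so it never exceeds 11. At the worst case, ρ = 0, the noncentrality is 6 / (11 × √(2/n)):
- m = 21: 3.66, power 90.8%.
- m = 16: 3.31, power 84.7%.

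At ρ = 0.5, m = 21, power is 96.7%.

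**SBP below 140.** p = Φ((140 − mean)/11), with mean = baseline − 5 (control) or baseline − 11 (intervention). The noncentrality is (p₁ − p₀) / √([p₀(1 − p₀) + p₁(1 − p₁)]/n), on 10 df.

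| Baseline mean | Control p₀ | Intervention p₁ | Power, m = 21 | Power, m = 16 |
|---|---|---|---|---|
| 150 | 0.32 | 0.54 | 75.3% | 66.9% |
| 155 | 0.18 | 0.36 | 68.9% | 60.4% |
| 160 | 0.09 | 0.21 | 55.2% | 47.4% |

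**Gap.** m = 21: 90.8 − 75.3 = 15.5 to 90.8 − 55.2 = 35.6 points. m = 16: 84.7 − 66.9 = 17.8 to 84.7 − 47.4 = 37.3 points.

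**Sensitivity to the difference.** The Primary objective implies 10 − 5 = 5 mmHg. At m = 21 this gives 78.4% against 59.1, 52.4 and 40.3%.

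**Unadjusted change score.** With equal SDs at both times, its SD is 11 × √(2(1 − ρ)), which exceeds 11 whenever ρ is below 0.5. At ρ = 0 it is 15.6, and power is about 65% at m = 21 and 56% at m = 16. The cut at 140 then does better at baselines of 150 and 155, and worse only at 160.

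**The case against.** The strongest reply is that nothing in item d is wrong. The cut is the trial's own entry threshold, so the proportion answers a natural question: how many newly diagnosed hypertensives are brought under control? Item d is also the only planned test that involves diastolic pressure, so replacing it outright would remove diastolic control from the tests. This stands, and it is why the rate should be kept.

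A reader might infer that the chi-square test costs a fixed 15 to 37 points of power against mean SBP change. The article does not support that. The range needs an assumed baseline mean, one SD for both scales and a cluster adjustment that item d does not mention. If the tests ran with no design effect on 126 per arm, the loss against a t-test with SD 11 would be 6 to 19 points for 6 mmHg, over assumed control rates of 10 to 70%. If the SD of change is 15.6, the chi-square can be the better test. That reading is not far-fetched: it brings the stated 94% power for the whole trial within reach (93.4% at 57 per cluster). The advantage survives it only when the comparison adjusts for baseline.

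A reader might also infer that the trial's blood pressure conclusion is at risk. It is not: item a is continuous and includes the diabetics, and no objective or power claim rests on item d. Finally, an analysis plan that is not shown may add continuous subgroup results. That limits the weight of the point, but item d as published names the test and its significance rule.

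**Conclusion.** The point holds as a minor one about the choice of analysis. Item d is the subgroup's only stated blood pressure test, leaves out baseline, departs from the scale used for the article's blood pressure aims, and answers no stated objective. The stated inputs, with the assumptions listed, give a baseline-adjusted SBP comparison at least 91% power at 21 per cluster against about 55 to 75% for SBP below 140, and at least 85% against about 47 to 67% at 16 per cluster.

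These are illustrations rather than limits. They rest on 11 mmHg being the SD of final SBP, on a mean baseline of 150 to 160 mmHg, and on a systolic-only version of the cut, because the article gives no diastolic inputs. None of them is the power of the planned test on 140/90 itself. The direction is dependable for the baseline-adjusted comparison under these assumptions, but not for a simple change score.

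**What to change.** Reword item d along these lines: in patients with type 2 diabetes, SBP at 15 months will be compared between arms with adjustment for baseline SBP, handling clusters as for the primary outcome; the proportion with BP below 140/90 will be reported by arm with a confidence interval as a supplementary result.

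Keeping the proportion means diastolic control is still reported, and the 140/90 threshold is untouched. The cost is one extra model and a few words of text, with no new data or patients. The small downside is that the easily read control rate becomes supplementary in this subgroup. The inception and piloting phase already provides for revising the statistical methods, so the change fits there.
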